## Abstract

**Background:**

Laparoscopic cholecystectomy is the gold standard for treating symptomatic gallstone disease. Pneumoperitoneum is essential for adequate visualization during the procedure and is typically maintained at a standard pressure of 12–14 mmHg. However, high insufflation pressure may contribute to increased postoperative pain. This study aims to assess whether low-pressure pneumoperitoneum (8 mmHg) reduces postoperative pain compared to standard pressure (14 mmHg), without compromising operative safety or efficacy. We hypothesize that low pressure pneumoperitoneum at 8 mmHg reduces postoperative pain, without increasing operation time or postoperative morbidity.

**Methods:**

This is a single-center, randomized, controlled, double-blind trial. Consecutive Adult patients scheduled for elective laparoscopic cholecystectomy will be randomized in a 1:1 ratio to receive either low-pressure (8 mmHg) or standard-pressure (14 mmHg) pneumoperitoneum. The primary outcome is postoperative abdominal pain assessed using the Visual Analog Scale (VAS) at 6 hours after surgery. Secondary outcomes include VAS pain scores at 12 and 24 hours, postoperative nausea and/or vomiting, postoperative hospital stay and postoperative 30-day morbidity. The enrollment of patients will be done between November 12, 2024 to December 31, 2025.

**Trial registration:**

ClinicalTrials.gov NCT06685250

**Conclusion:**

If proven effective, low-pressure pneumoperitoneum may represent a simple strategy to improve postoperative comfort in laparoscopic cholecystectomy without compromising surgical outcomes.

## Introduction

Laparoscopic cholecystectomy is the gold standard for symptomatic gallstones [1]. It involves the use of Carbone dioxide to inflate the peritoneal cavity to create a pneumoperitoneum in order to provide an adequate visualization and a sufficient space for working. There is no consensus on the optimal pressure of the pneumoperitoneum, but the standard varies between 12 and 14 mmHg [2]. Different studies have demonstrated that high pneumoperitoneum pressure is associated with postoperative morbidity, particularly cardiopulmonary complications and postoperative pain [3]. For this reason, the low impact surgery concept has emerged [4]. Several meta-analyses have compared low pressure versus standard pressure in laparoscopic cholecystectomy and the results were controversial, with high risk of bias across studies [2,5].

### Aim

We aimed to compare postoperative pain (low pressure 8 mmHg versus high pressure 14 mmHg), as a primary outcome, in patients undergoing laparoscopic cholecystectomy for uncomplicated gallbladder lithiasis.

### Hypothesis

The low pressure pneumoperitomenum at 8 mmHg reduces the postoperative pain, at postoperative 6th hour assessment, in patients undergoing laparoscopic cholecystectomy, compared to pneumoperitoneum at 14 mmHg.

## Methods

### Design

This is a single-center prospective randomized controlled trial, double-blinded, parallel-group trial involving patients requiring laparoscopic cholecystectomy for uncomplicated gallbladder lithiasis. The expected start and end dates for this study are November 12, 2024 and December 31, 2025.

This protocol has been developed in accordance with the Standard Protocol Items: Recommendations for Interventional Trials (SPIRIT) guidelines and checklist (attached S1 File) [6]. The study was registered on the ClinicalTrials.gov within the number **NCT06685250 on November 11, 2024** (attached S2 File).

### Study setting

Recruitment will take place at department B of general surgery of Charles Nicolle university hospital of Tunis, Tunisia. This department performs a minimum of six laparoscopic cholecystectomy (LC) per week (for complicated and uncomplicated gallbladder lithiasis).

### Study population

Consecutive patients admitted for laparoscopic cholecystectomy for uncomplicated gallbladder lithiasis will be assessed for eligibility. Screening and enrolment will proceed until the target number of participants is reached.

### Eligibility criteria

**Inclusion criteria:** (consecutive if possible) adult patients (≥18 years) with uncomplicated symptomatic gallbladder lithiasis scheduled for elective surgery (ASA 1 or ASA 2)**NON Inclusion criteria:** Were not included patients with: choledocholithiasis, associated surgical procedures, cerebrovascular accident (with neurological sequelae or other neurological disorders that affect sensation of pain), ascites, carcinomatosis**Exclusion criteria: were patients who had** conversion to laparotomy **or** need to keep an Escat’s drain

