### Randomization

Prior to enrolment, all inclusion and exclusion criteria will be thoroughly assessed. Eligible participants will be randomly assigned to one of two parallel groups using **block randomization with a fixed block size of four**, to ensure a progressive balance between arms throughout the inclusion period.

The randomization sequence was generated using a **table of random numbers** extracted from the reference textbook L’essai thérapeutique chez l’homme by Schwartz D et al, [7]. Allocated study subjects were randomly assigned by, using simple 1:1 non-stratified sequence and a block size of 4 [7].

Allocation was implemented sequentially, according to the randomization list, by a team member **not involved in outcome assessment**, in order to maintain **allocation concealment** and minimize the risk of selection bias.

The timeline for enrolment, intervention and assessments is outlined in the SPIRIT schedule of events in Fig 1

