### Data collection

#### Baseline assessment (at admission).

Prior to group allocation, each participant’s sociodemographic data (such as age, gender, Body Mass index), baseline characteristics including comorbidities, American Society of Anesthesiologist (ASA) score, preoperative clinical examination, preoperative biological tests, preoperative ultrasound data, and surgical exploration data after trocar placement will be recorded.

Following this assessment, participants will be randomized into one of two study groups.

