#### Statistical analysis.

All statistical analyses will be conducted in the intention-to-treat population at a two-sided 5% alpha risk. For each group and at each assessment time, categorical variables will be summarized as numbers and percentages, and continuous variables will be expressed as number, mean, and standard deviation (SD). Quantitative variables with skewed distribution will be presented in terms of median and interquartile range (IQR) (25th-75th percentile).

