### Secondary endpoints

**Change of VAS over time:** To evaluate the temporal evolution of VAS (at H6, H12 and H24), analysis of variance (ANOVA) with Bonferroni adjustment will be performed. This statistical approach is particularly suited to repeated measures data.Nausea and vomiting: Changes from baseline (H0) to the final time point (H4) will be analyzed within groups using paired ANOVA tests. Between-group comparisons of these changes will be performed using independent ANOVA tests.Duration of hospital stay: the mean hospital stays in each group (control vs intervention) will be compared using t-tests or non-parametric test U of Mann and Whitney when appropriate.Operative time: the mean operative time in each group (control vs intervention) will be compared using t-tests or non-parametric test U of Mann and Whitney when appropriate.Conversion rate: the frequency of conversion rate in each group will be compared by chi²test or fisher exact test when appropriate.30-day morbidity: the frequencies of each postoperative complication in each group will be compared by chi²test or fisher exact test when appropriate.

The statistical analysis will be conducted using SPSS version 26. Analyses will be performed by an independent investigator (CD in the authors’ list) blinded to treatment allocation, ensuring unbiased interpretation of the data.

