#### Data analysis framework.

All analyses will follow the intention-to-treat principle. The primary outcome (VAS pain score at 6 hours) will be compared between groups using an independent t-test or a Mann–Whitney U test if non-normal. An adjusted analysis using ANOVA will be performed with age, sex, BMI, ASA class, and operative time as covariates. Repeated measures of pain (6, 12, and 24 hours) will be analyzed using analysis of variance (ANOVA) with Bonferroni adjustment. Categorical variables, including postoperative nausea and vomiting and complications, will be compared using χ² or Fisher’s exact tests. Continuous secondary outcomes will be analyzed using t-tests or appropriate non-parametric methods. Missing data will be addressed using multiple imputation (fully conditional specification with predictive mean matching), with sensitivity analyses including complete-case and per-protocol analyses. All tests will be two-sided with a significance level of 0.05. Statistical analyses will be performed using SPSS version 26.

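### Excluding patients for conversion or a kept Escat's drain contradicts intention-to-treat and the conversion endpoint, and can bias the comparison if applied to randomised patients

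*Protocol article*

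**What the plan says.** The Eligibility criteria section of the protocol has two separate negative lists. The non-inclusion list concerns conditions at entry ("Were not included patients with: choledocholithiasis, associated surgical procedures", and others). The exclusion list names two events of the operation itself: "conversion to laparotomy" and "need to keep an Escat’s drain".

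Four other parts of the protocol bear on this:

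- Randomization: "Prior to enrolment, all inclusion and exclusion criteria will be thoroughly assessed".
- Baseline assessment: the data to be recorded before allocation include what is found at exploration once the trocars are in. Then: "Following this assessment, participants will be randomized into one of two study groups".
- Statistical analysis: "All statistical analyses will be conducted in the intention-to-treat population at a two-sided 5% alpha risk". The Data analysis framework repeats the principle and plans multiple imputation "with sensitivity analyses including complete-case and per-protocol analyses".
- Secondary endpoints: conversion to open surgery is listed as an endpoint, and the analysis section states that "the frequency of conversion rate in each group will be compared by" a chi-square or Fisher exact test.

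**The concern.** A patient who is converted, or who keeps an Escat's drain, has usually been randomised already and has been operated on at the allocated pressure. The Blinding section says that the surgeon knows the allocation. The exclusion can therefore depend both on the treatment and on decisions taken in knowledge of it. Reduced exposure at 8 mmHg is a plausible route to conversion. That is a reviewer's argument, however, and the protocol gives no data on it.

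Three things are at stake:

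- The analysis population is undefined, because two rules in the same document give different sets of patients.
- Conversion is an endpoint that the exclusion rule would remove from the data.
- The trial also hypothesises no increase in operating time or morbidity at low pressure, and converted patients are among those most informative about that.

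If more patients were removed from the low-pressure arm, and those patients had more pain, longer operations, longer stays or more complications, the remaining comparison would favour low pressure.

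**Working it through.** **Do the rules conflict?**

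1. The exclusion list is separate from the non-inclusion list and is worded for events that have occurred, so it acts after entry. The data collection section records Escat's drain placement during the operation.
2. Randomisation precedes most of the operation on either account of its timing. The baseline section puts it after exploration through the trocars. The trial implementation section has the envelope opened after consent and confirmed eligibility. The allocated pressure starts once the ports are placed.
3. A check before enrolment therefore cannot cover these two criteria.
4. Intention-to-treat keeps these patients and the exclusion list removes them. Both cannot be followed.
5. If converted patients are removed before conversions are counted, both numerators are 0 and the chi-square or Fisher test carries no information. If they are kept, the exclusion has no effect.

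**The plan's own sample size**

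Inputs from the sample size section: difference 1, SD 1.8, two-sided 5%, power 90%.

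- Normal approximation: n = 2 × (1.960 + 1.282)² × 1.8² / 1² ≈ 68.1, so 69 per arm. The exact t-test solution is 69.06, so 70 per arm. The stated 70 per arm is reproduced.
- With all 85 per arm analysed, power for a 1-point difference is about 95%.

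**Possible size of the shift at 6 hours**

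Let c0 and c1 be the excluded shares at 14 and 8 mmHg, and d the excess VAS of excluded over retained patients, taken as equal in both arms. The mean of all randomised patients in an arm is the retained mean plus c × d. Removing the excluded patients therefore shifts the difference towards low pressure by (c1 − c0) × d. The protocol gives none of these inputs, so all are assumed.

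| c0 | c1 | d | shift (points) |
|---|---|---|---|
| 2% | 2% | any | 0 |
| 2% | 4% | 2 | 0.02 × 2 = 0.04 |
| 2% | 6% | 3 | 0.04 × 3 = 0.12 |
| 3% | 9% | 2 | 0.06 × 2 = 0.12 |
| 3% | 9% | 3 | 0.06 × 3 = 0.18 |

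In patients, 2% of 85 is 1.7 and 6% is 5.1; 3% is 2.6 and 9% is 7.7.

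**What such a shift does to the test**

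The standard error is 1.8 × √(2/85) = 0.276. With no true difference, the type I error is Φ(−1.96 + shift/SE) + Φ(−1.96 − shift/SE).

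- Shift 0.04 (0.14 SE): about 5.2%.
- Shift 0.12 (0.43 SE): about 7.2%.
- Shift 0.18 (0.65 SE): about 10%.

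More extreme assumptions, with the standard error computed on the reduced numbers, give 8.7% (2% versus 10%, d = 2, shift 0.16) and 17.7% (5% versus 15%, d = 3, shift 0.30). Power for a 1-point difference remains about 93-95% in the scenarios with the exclusion applied. The problem is bias, not lost power.

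**The case against.** The strongest reply is that intention-to-treat is stated for all analyses, and conversion is explicitly compared by group. On that reading, conversions are counted among all randomised patients and the exclusion list is a careless remnant or describes the per-protocol set. The protocol also records Escat's drain placement and keeps a log of deviations and incidents, so nothing shows that these patients vanish from the data. This stands as far as it goes. A reader might infer that the conversion table must be 0/85 versus 0/85 whatever happens. That follows only if the exclusion list overrides intention-to-treat, and removed patients would then also lower the denominators.

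A reader might also infer that the primary comparison is biased, or that randomisation is lost. The protocol does not support that. It gives no rates and no pain scores for such patients, and the population is elective, uncomplicated and ASA 1 or 2. Equal exclusion rates with equal excess pain give no shift.

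Three further limits stand:

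- A conversion decided at exploration could precede allocation and would then be a legitimate exclusion. The exclusion list is not restricted to that window.
- A complete-case analysis does not by itself drop converted patients who have a 6-hour score. It fails to show the problem only if they were removed beforehand.
- The Escat's drain is recorded separately from other drainage. The protocol does not link it to pressure or to pain, so the argument is weaker for it than for conversion.

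None of this settles which rule governs.

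**Conclusion.** The contradiction is established from the protocol's own text. The exclusion rule is wrong as written, and this is not a detail that can be left to an analysis plan. Applied to the analysis set, it empties the conversion comparison and can bias pain, operative time, stay and morbidity.

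The size of any bias is unknown. Under the assumed rates above, the 6-hour shift runs from zero to 0.18 points, at most 18% of the planned 1-point difference. These figures assume more exclusions at low pressure and 2 to 3 points more pain in excluded patients, neither of which the protocol supports or rules out. The case for changing the text rests on the undefined population and the conversion endpoint as much as on the possible shift in pain.

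**What to change.** - Replace the exclusion sentence with a statement that every randomised patient stays in the allocated arm, is followed for pain at 6, 12 and 24 hours and for all other outcomes, and is counted in the conversion rate.
- Use conversion and a kept Escat's drain only to define the per-protocol sensitivity set.
- Report kept Escat's drains by arm beside conversions. Placement is already recorded.
- Allow exclusion only where the event was decided before allocation.
- Retrieve the 6-hour scores of any randomised patient already excluded.

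An extra sensitivity analysis giving such patients an unfavourable value when their score is missing is optional, since multiple imputation and sensitivity analyses are already planned.

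The cost is protocol wording and some retrieval of scores from inpatients. No treatment changes, and power with 85 per arm is about 95%. The downside is that the estimate may become slightly less favourable to low pressure. The trial is under way, so the rule should be settled before the allocation is unblinded for analysis.

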### Intervention

#### Standard of care.

In all patients, gas pressure was set to 12 mmHg during placement of four ports. Later on, in the high-pressure group the procedure was performed at 14 mm Hg and in the low-pressure group the procedure was performed at 8 mmHg pressure.

Postoperative analgesia will be delivered to all patients respecting the same protocol: 1g of paracetamol/IV which will be administered 30 minutes before the end of the intervention.

#### Control group: standard pneumoperitoneum pressure 14mmHg.

CO2 pneumoperitoneum insufflation at standard pressure (14 mmHg) throughout the procedure

#### Intervention group: low pneumoperitoneum pressure 8 mmHg.

Insufflation of pneumoperitoneum with low-pressure CO2 (8 mmHg) after introduction of standard-pressure trocars

#### Strategies to improve adherence to interventions.

To ensure adherence to the intended stable pneumoperitoneum throughout the intervention, several measures will be implemented. The gas circuit, including the tightness of the insufflation pipe and filters, will be checked before starting the intervention. The healthcare professional administering the intervention, part of the core team of senior physicians and the operating room nurse, will supervise each session.

### Informed consent

Written informed consent will be obtained from all eligible participants. The investigators will explain the study to each potential participant, provide them with an informed consent form, and answer any questions they may have. Written informed consent will be obtained from each participant prior to enrolment (attached S3 File).

### Randomization

Prior to enrolment, all inclusion and exclusion criteria will be thoroughly assessed. Eligible participants will be randomly assigned to one of two parallel groups using **block randomization with a fixed block size of four**, to ensure a progressive balance between arms throughout the inclusion period.

The randomization sequence was generated using a **table of random numbers** extracted from the reference textbook L’essai thérapeutique chez l’homme by Schwartz D et al, [7]. Allocated study subjects were randomly assigned by, using simple 1:1 non-stratified sequence and a block size of 4 [7].

Allocation was implemented sequentially, according to the randomization list, by a team member **not involved in outcome assessment**, in order to maintain **allocation concealment** and minimize the risk of selection bias.

The timeline for enrolment, intervention and assessments is outlined in the SPIRIT schedule of events in Fig 1

**Fig 1 pone.0339161.g001:**
[figure not shown]
SPIRIT schedule of enrollment.

The Flowchart of the investigation is illustrated in Fig 2.

**Fig 2 pone.0339161.g002:**
[figure not shown]
SPIRIT Flow diagram for patients included in the randomized controlled trial comparing postoperative pain after laparoscopic cholecystectomy with standard (14 mmHg) versus low pressure pneumoperitoneum (8mmHh).

### Blinding

The study will follow the principles of the double blinding Randomized Controlled trials [8], which is specifically intended to minimize bias in outcome assessment and data analysis.

To maintain blinding integrity and minimize bias, the participant and the assessor of the postoperative pain were blinded for the allocation. Only the surgeon, the anesthetist and the operating room nurse responsible for opening the allocation envelope and administering the assigned intervention will be aware of the group assignment. These persons will not be involved in outcome assessment, clinical follow-up, or data analysis. The outcome assessor will be a trainee resident. All outcome assessors, trained residents not involved in randomization or intervention delivery, will remain blinded to group allocation throughout the study. Similarly, data analysts will be blinded to treatment assignment to ensure objectivity in statistical analyses and interpretation of results. Anesthetist and surgeon will be explicitly instructed not to disclose their group allocation to any member of the clinical or research team involved in follow-up or outcome assessment. This approach is designed to preserve the integrity of the blinding process and uphold the internal validity of the trial.

### Data collection

#### Baseline assessment (at admission).

Prior to group allocation, each participant’s sociodemographic data (such as age, gender, Body Mass index), baseline characteristics including comorbidities, American Society of Anesthesiologist (ASA) score, preoperative clinical examination, preoperative biological tests, preoperative ultrasound data, and surgical exploration data after trocar placement will be recorded.

Following this assessment, participants will be randomized into one of two study groups.

#### During laparoscopic cholecystectomy.

The presence of eventual adhesions, difficult dissection, bleeding, biliary injury, realization of cholangiography, placement of Escat’s drain, placement of drainage, operation time were recorded.

#### Postoperative assessment.

The postoperative pain at 6th, 12th, 24th hours, the presence of nausea and/or vomiting, the consumption of painkillers, the duration of hospital stay, the presence of eventual complications within 30 days were recorded.

#### Trial implementation and coordination.

The rigorous implementation of this trial relies on strict protocol adherence clearly defined roles and standardized procedures to ensure methodological integrity and internal validity. Prior to enrolment, all department B of general surgery medical and paramedical staff will be trained on the study protocol and data collection methods during dedicated briefing sessions.

The randomization sequence will be generated by (CD) not involved in recruitment, intervention delivery, or outcome assessment. Daily screening and enrolment of eligible participants will be carried out by site investigators. After obtaining written informed consent and confirmation of eligibility, the senior surgeon will perform the allocation by opening sealed, opaque envelopes containing the group allocation, serving as the **sole custodian** of the envelopes. Participants assigned to the intervention group will be operated under 8 mmHg pneumoperitoneum pressure. Control group participants will be operated under pneumoperitoneum pressure (14 mmHg). All patients will receive 1g of intravenous paracetamol 30minutes before the operation’s end. Outcome assessments will be conducted by well-trained residents who are blinded to participants’ group assignments and data analysis. To minimize bias, these residents will not be involved in recruitment or intervention delivery. All assessors will undergo specific training to standardize data collection procedures and reduce inter-rater variability.

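### The senior surgeon holds and opens all envelopes under a disclosed fixed block of four, so up to a third of allocations can be deduced, and two sections disagree on who opens them

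*Protocol article*

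**What the plan says.** The relevant statements are spread over four sections of the protocol article.

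- **Randomization.** The method is "block randomization with a fixed block size of four", described again as "using simple 1:1 non-stratified sequence and a block size of 4". On who carries it out: "Allocation was implemented sequentially, according to the randomization list, by a team member" who takes no part in assessing outcomes. The section presents this separation as the means of keeping allocation concealed.
- **Trial implementation and coordination.** Site investigators screen and enrol. After consent and confirmation of eligibility, "the senior surgeon will perform the allocation by opening sealed, opaque envelopes containing the group allocation". The same surgeon is the "sole custodian" of the envelopes.
- **Blinding.** Knowledge of the assignment is restricted: "Only the surgeon, the anesthetist and the operating room nurse responsible for opening the allocation envelope and administering the assigned intervention will be aware". These people are kept out of outcome assessment, follow-up and analysis. Recruitment and eligibility are not on that list.
- **Baseline assessment.** Among the data gathered before randomization, "surgical exploration data after trocar placement will be recorded". Randomization follows.

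The trial is single-centre, and Trial status says that it was under way when the article was published.

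**The concern.** Allocation concealment means that nobody who can influence whether or when a patient enters the trial can foresee the next assignment. Sealed opaque envelopes hide the contents of the next one. They do not prevent its being inferred from the previous ones when blocks are short, of constant and known size, and drawn from a single list. The person best placed to make that inference is whoever opens each envelope, and in this plan that person also keeps the unopened ones.

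The reason given for concealment does not address this. Keeping the allocator away from outcome assessment protects the pain score from biased measurement. Concealment needs separation from recruitment and eligibility. Trial implementation and coordination applies that separation to the person generating the sequence and to the assessing residents, but not to the senior surgeon.

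What is at stake is comparability at entry. If patients expected to have a difficult operation were steered by a predicted assignment, the arms would differ before treatment, and blinded scoring at six hours could not undo it.

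**Working it through.** **Inputs.** Block size 4, ratio 1:1, one unstratified list (Randomization); 170 patients (Sample size and power). The article gives no predictability figure, so there is none to reproduce. The figures below apply to an observer who knows the block size, all earlier allocations and where each block starts.

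**Share of assignments that are certain.** With L for low and S for standard pressure, a block is one of six equally likely sequences: LLSS, LSLS, LSSL, SLLS, SLSL, SSLL. An assignment is certain when only one arm remains in the block.

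| Position in block | Probability that it is certain | Probability that the best guess is right |
|---|---|---|
| 1 | 0 | 1/2 |
| 2 | 0 | 2/3 |
| 3 | 2/6 = 1/3 (LLSS, SSLL) | 1/3 × 1 + 2/3 × 1/2 = 2/3 |
| 4 | 1 | 1 |

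- Certain: (0 + 0 + 1/3 + 1)/4 = 1/3, which is 8 of the 24 positions.
- Best guess right: (1/2 + 2/3 + 2/3 + 1)/4 = 17/24 = 70.8%, against 50% with no information.

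**Applied to this trial.** 170 = 42 × 4 + 2.

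- Expected certain assignments: 42 × 4/3 = 56, and none in the last two patients; 56/170 = 32.9%.
- Expected correct guesses: 42 × 17/6 + 1/2 + 2/3 = 119 + 1.17 = 120.2; 120.2/170 = 70.7%, against 85 by chance.

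**What block size alone would change.** The same enumeration for a fixed block of 6 gives 1/4 certain and 41/60 = 68.3% guessed correctly. Equal numbers of blocks of 4 and 6 with known boundaries give (4 × 1/3 + 6 × 1/4)/10 = 28.3% certain. Varying the size therefore helps mainly if the sizes are not disclosed, and separating custody matters more.

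**Who opens the envelope.** Trial implementation and coordination names the senior surgeon. In Blinding the natural reading is "the operating room nurse responsible for opening the allocation envelope", although grammatically the clause could cover the surgeon and anesthetist as well. Randomization mentions no envelope and no opener, only a team member working from a list. The conflict is thus between two sections; the third leaves both the role and the mechanism (list or envelopes) unspecified.

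**The case against.** The strongest reply is that the safeguards are better than this makes them look. Site investigators enrol, and allocation comes after consent, confirmed eligibility and exploration. Allocation is sequential, the envelopes are sealed and opaque, and patient and assessor are blinded. The adjusted analysis includes age, sex, BMI and ASA class. Operational detail such as envelope numbering may be in a fuller protocol that is not shown. Much of this stands: it narrows the route to bias. It does not close it, because the article nowhere keeps the custodian out of screening, scheduling or exploration, and adjustment cannot remove selection on unmeasured factors.

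Several stronger readings are tempting and are not supported:

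- *Three sections name three different openers.* Randomization names none, and its team member could be the senior surgeon.
- *A third of allocations are known in advance.* They can be deduced by someone who tracks the list. One third is a ceiling.
- *The surgeon knows past allocations from having operated on everyone.* The article does not say that one surgeon performs every operation; the adherence section speaks of a core team of senior physicians. The knowledge comes from opening the envelopes.
- *The surgeon makes the final eligibility decision.* The article does not say who decides or that eligibility is reopened at exploration. It only fails to exclude the surgeon.
- *A patient could be deferred on the exploration findings.* With the ports in place this is implausible; any deferral would have to occur at scheduling.
- *A patient could be given a different envelope.* That would be tampering, which varying block sizes would not prevent, and nothing suggests it.

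**Conclusion.** The point holds as a weakness in concealment. One unblinded person keeps and opens the envelopes under a disclosed fixed block of four, and could deduce up to about one third of assignments (33.3%; about 56 of 170) and guess 70.8% correctly. The stated safeguard protects blinding and leaves concealment uncovered. Two sections disagree on the opener.

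The figures assume that the senior surgeon opens every envelope, that block boundaries can be followed, and that the list is used in order. If the nurse opens the envelopes or the role rotates, the surgeon's share lies between zero and one third, depending on what is shared among staff. The figures measure predictability. They do not measure bias in the six-hour pain score, which cannot be derived from the article. No misconduct is implied. The change is worth making because it is cheap and because selection at entry cannot be reliably corrected afterwards.

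**What to change.** 1. Give custody of the envelopes to an existing team member who neither recruits nor operates.
2. Have the next envelope in sequence opened only after eligibility has been recorded as final.
3. For any patients not yet randomized, regenerate the list from the end of the current block with randomly varying block sizes, for example 4 and 6, not disclosed to site staff.
4. Make Randomization, Blinding, and Trial implementation and coordination describe this one procedure: who holds the envelopes, who opens them and when. Justify concealment by separation from recruitment and eligibility.
5. For patients already randomized, report who held and who opened the envelopes, and that the block was fixed at four.

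The cost is re-issuing the remaining envelopes and a wording amendment. The arms may temporarily differ by up to 3 patients instead of 2, which is negligible at 85 per arm. Items 1 to 3 help only patients not yet randomized. Trial status expects recruitment to finish by December 2025, so they may be few, and the number is not given. Items 4 and 5 are useful whatever that number is.
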